##### Primary outcome: cognitive frailty

This study operationalized cognitive frailty as proposed by Kelaiditi et al. (17) using Fried's criteria as outlined in the Cardiovascular Health Study to define physical frailty and the Clinical Dementia Rating Scale (CDR) to define objective cognitive impairment. The presence of one or two of the Fried's criteria was defined as pre-frailty, whilst the presence of three or more was defined as frail and a score of 0.5 on the CDR is defined as mild cognitive impairment (MCI) (17). Collectively, participants who had a combination of pre-frailty/frailty and MCI were categorized as cognitive frailty (Table 1).

**Table 1 T1:** Classification of cognitive frailty groups.

	**Criteria**	**Categorization**		
		**Robust**	**Cognitive pre-frailty**	**Cognitive frailty**
**Frailty** Fried et al. (6)	*Shrinking*: Unintentional weight loss of more than 5 kgs	0	1–2 Criteria	≥3 Criteria
	*Weakness*: Assessed with hand grip strength and adjusted for gender and body mass index against original cut-off points.			
	*Slowness*: Assessed with 5-meter gait speed test, adjusted for gender and height against original cut off points.			
	*Exhaustion*: Identified with two items from the CES-D scale.			
	*Low physical activity*: Identified by low scores of the PASE.			
**Cognitive impairment** Kelaiditi et al. (17)	Clinical Dementia Rating Scale score	0	0.5	0.5

*CES-D, Center for Epidemiologic Studies Depression Scale; PASE, Physical Activity Scale for Elderly*.

##### Secondary outcomes

Sociodemographic information, Clinical Characteristics and Lifestyle: Sociodemographic and lifestyle variables included age, gender, level of education, ethnicity, marital status, status of employment, income status, alcohol consumption and smoking history. Clinical characteristics included history of falls, family history of dementia and history of chronic diseases.

Physical Fitness and Functional Status: The senior fitness test by (49) was used to measure physical fitness. Thirty-Second Chair Stand test for lower body strength assessment; Back Scratch test for upper body flexibility assessment; Sit-and-Reach test for lower body flexibility; Timed Up and Go test for mobility and balance; 6-meter Gait Speed test for gait speed; and the 2-Min Step test to assess cardiovascular fitness and endurance. Functional status was assessed by level of independence based on the Instrumental Activities of Daily Living (IADL) (50).

Cognitive Function: The Mini Mental Examination State (MMSE) was used to assess global cognition (51). The Rey Auditory Verbal Learning Test (RAVLT) was used to detect short-term verbal memory, working memory, verbal learning and declarative memory (52). The Digit Span test, originally a test from Weschler Adult Intelligence Scale (WAIS) assessed memory, attention and concentration (53). The Trails Making Test (TMT) was used to assess processing speed and mental flexibility (54).

Nutritional Status: Anthropometric measurements and body composition were used as indicators of nutritional status. Length of arm demi-span, mid-upper arm circumference, waist circumference, hip circumference, and calf circumference were measured using the Lufkin^®^ W606PM Anthropometric Tape Measure. Body composition including body mass index, metabolic age, fat percentage (%), fat mass (kg), fat free mass (kg), and muscle mass (kg) was measured using the Tanita^®^ TBF-400 Total Body Composition Analyzer.

Dietary Intake: Dietary intake was assessed using the Dietary Habits Questionnaire (DHQ) to estimate the overall dietary intake, usual dietary habits and the mean intake of various types of nutrients (55). The food intake will be analyzed using Nutritionist-Pro software to estimate the total calories, macronutrients and micronutrients intake.

Psychosocial Status: The Geriatric Depression Scale-15 (GDS) was used to detect symptoms of depression (56). Domains of functioning and disability was assessed using the WHODAS 2.0 (57).

Quality of Life: The 15-D was used as a measure of health-related quality of life (HRQoL). It describes the participants' self-perception of the following domains: mobility, vision, hearing, breathing, sleeping, eating, speech, excretion, usual activities, mental function, discomfort and symptoms, depression, distress, vitality, and sexual health (58).

##### Randomization

Participants with cognitive pre-frailty or cognitive frailty were randomized into intervention and control groups. Simple randomization was executed using the Research Randomizer computer program by the primary research coordinator (59). The trial flow is as illustrated in Figure 1. In this single blinded study, research assistants involved in data collection for the baseline and follow up outcome measures to prevent bias were blinded of the groups. Primary research coordinator was not involved in data collection. In order to minimize contamination between the intervention and control groups, an arrangement was made with the participating PAWEs to allow private and scheduled use of the facility on days that are not open for member activities.

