#### Data Analysis

All statistical analyses will be carried out using the Statistical Package for Social Sciences (SPSS) software, version 23.0. An alpha level of (0.05) was considered for all the statistical tests used in the study. Two-sided *p* values of (0.05) and (80%) power will be statistically significant. Results of the randomized controlled trial will be analyzed using repeated measures analysis of variance for pre-test (Baseline Scores) and post-test (3rd month, 6^th^ month) for experimental and active control group. *Post-hoc* analysis will be conducted using Benferonni correction. Analysis will include nutritional assessment, cognitive frailty outcome measures, cognitive assessments, physical function assessments and quality of life.

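### The named analysis of cognitive frailty status cannot use the number of Fried criteria at entry, so chance imbalance in that count enters the estimate and a little power is lost

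*Protocol article*

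**What the plan says.** All references are to the protocol article.

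- **Randomization.** "Participants with cognitive pre-frailty or cognitive frailty were randomized into intervention and control groups", and "Simple randomization was executed using the Research Randomizer computer program by the primary research coordinator". No stratification factor, blocking or minimization is named.
- **Primary outcome: cognitive frailty.** On the physical side: "The presence of one or two of the Fried's criteria was defined as pre-frailty, whilst the presence of three or more was defined as frail". On the cognitive side, a Clinical Dementia Rating (CDR) of 0.5 defines mild cognitive impairment. The two are then combined: "Collectively, participants who had a combination of pre-frailty/frailty and MCI were categorized as cognitive frailty". Table 1, by contrast, keeps three levels: robust, cognitive pre-frailty (1–2 criteria) and cognitive frailty (3 or more).
- **Abstract.** The primary outcome is cognitive frailty status, the aim is reversal, and baseline values come from the screening visit.
- **Data Analysis.** "Results of the randomized controlled trial will be analyzed using repeated measures analysis of variance", with baseline scores as the pre-test and months 3 and 6 as the post-test. Cognitive frailty outcome measures are among the variables covered. No severity covariate is named.

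**The concern.** Participants enter with anything from one Fried criterion upwards. To become robust on the physical side, a person must lose every criterion present at entry, so the entry count plausibly predicts that route out of cognitive frailty. It is recorded for everyone before allocation.

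As described, neither the allocation nor the analysis uses it when status is compared between arms. Two things follow. If one arm happens to receive people with more criteria, the unadjusted difference in status carries that imbalance. And variation that a baseline covariate could explain stays in the error, which costs power.

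**Working it through.** **1. Does the pre-test term already carry entry severity?**

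Let S be merged status, with 1 for pre-frail or frail plus CDR 0.5. Eligibility requires cognitive pre-frailty or cognitive frailty, so S = 1 at baseline for everyone. The baseline-to-month-6 contrast between arms is

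mean(S6 − 1) in intervention − mean(S6 − 1) in control = mean(S6) in intervention − mean(S6) in control.

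That is the unadjusted comparison at follow-up; baseline cancels. On Table 1's three levels, baseline separates 1–2 criteria from 3 or more. The Introduction gives prevalences of 37.4% (cognitive pre-frailty) and 2.2% (cognitive frailty), so 37.4/39.6 = 94.4% of eligible people would share one baseline level and 2.2/39.6 = 5.6% the other. One criterion is not separated from two. Only if the Fried count itself were the analyzed variable would its baseline enter fully.

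**2. How large can chance imbalance be?**

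The article states no sample size, so N = 60, 100 and 200 are assumed, with 1:1 allocation. For a stratum with share q, the SD of the between-arm difference in share is about √(4q(1−q)/N); for example q = 0.5 and N = 100 give 0.10. Simulated probability of a difference of 10 points or more:

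| Stratum share | N=60 | N=100 | N=200 |
|---|---|---|---|
| 5.6% | 10% | 3% | 0.3% |
| 30% | 41% | 28% | 13% |
| 50% | 46% | 33% | 16% |

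For the mean count, take two assumed mixes of 1/2/3/4 criteria.
- Mix A (55/39/5/1%): mean 1.52, variance 2.72 − 1.52² = 0.41, SD 0.64. At N = 100 the SD of the difference is 0.64 × 2/√100 = 0.128, so a gap of 0.2 or more has probability about 12%.
- Mix B (45/41/10/4%): mean 1.73, variance 3.63 − 1.73² = 0.64, SD 0.80. The SD of the difference is 0.16, and the probability is about 21%.

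**3. Power, unadjusted against adjusted for entry count (two-sided 0.05)**

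Model 1 assumes reversal only by losing all k criteria: P = r^k, with r = 0.35 in control and 0.60 in intervention.

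| Mix | N=60 | N=100 | N=200 |
|---|---|---|---|
| A | 48→52% | 72→75% | 95→96% |
| B | 50→54% | 69→73% | 95→97% |

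Repeat runs put the gain between 1 and 5 points.

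Model 2 adds a CDR route: P = 1 − (1 − r^k)(1 − c). At N = 100:
- c = 0.20 control, 0.35 intervention: 77.3→78.2% (A) and 77.4→79.1% (B).
- c = 0.30 in both arms: 42.0→43.0% (A) and 37.5→38.8% (B).

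Over N = 60–200 the gain is about 0 to 2 points.

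Model 3 is a different construction: strata of 1, 2 and 3+ criteria, odds ratio 3, Mantel-Haenszel test with and without stratification by count.

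| Prognostic strength | N=60 | N=100 | N=200 |
|---|---|---|---|
| Weak, 6% at 3+ | 44→45% | 67→68% | 92→93% |
| Moderate, 15% at 3+ | 41→44% | 61→65% | 90→93% |
| Strong, equal thirds | 32→38% | 50→59% | 81→89% |

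The last row is a stress case, with a third of participants at 3+ against 5.6% from the article's prevalences.

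**4. Type I error**

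Under no effect, the unadjusted test in Model 3 rejected in 4.5–6.0% of trials overall and the stratified test in 4.4–6.0%, so both are nominal within simulation error. In Model 1 at N = 100, restricted to null trials whose mean counts differed by 0.2 or more, the unadjusted test rejected in 8.8% (A) and 7.4% (B), and the adjusted test in 4.7% and 5.1%.

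**The case against.** **The entry count is not the whole distance from reversal.** This stands. Merged status also needs CDR 0.5, so a return to CDR 0 ends it whatever the Fried count, and on Table 1's levels a fall from 3 criteria to 2 already changes category. A reader might infer that the count is the strongest predictor of reversal; the article gives nothing to support that. Model 2 shows the gain shrinking once a CDR route exists.

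**Simple randomization is valid.** This stands too. It is tempting to read the 7–9% rejection rates as an inflated false-positive rate. They apply only to null trials selected for imbalance; over all trials the error is nominal. Nor is a lopsided split of the frail group likely: with 6 frail people in 100, at least 5 fall in one arm with probability 2 × (6 + 1)/64 = 22%.

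**Baseline is in the model.** True of a three-level status in part, and of a Fried count in full. It does not help for the merged status, as step 1 shows.

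**Covariates may be listed in an analysis plan that is not shown.** A missing list would be no finding. The point here is narrower: the article names the model and defines the status, and together these leave the baseline term uninformative.

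**Stratified blocks would be the natural remedy.** They are not supported. The article describes randomization in the past tense; once the test is adjusted, stratified allocation adds only about 0 to 4 points; and the Intervention Providers section indicates that the coordinator who ran the randomization also delivers the intervention, so blocks would be more predictable to that person.

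**Conclusion.** The point holds in a limited form. The entry Fried count, which bears on the physical half of the primary outcome, is unused when merged status is compared between arms, and only partly used on Table 1's levels. The trial's validity is not in question.

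The cost is some precision, plus an estimate exposed to chance imbalance in entry count. Under the assumed mixes nearer the article's prevalences (Models 1 and 2, and the first two rows of Model 3), the power loss is about 0 to 5 points at N = 60–200, towards the bottom of that range when reversal through CDR is common. It reaches 6 to 10 points only in the equal-thirds, strongly prognostic case. Sample size, severity mix, reversal rates and treatment effect are all assumed, because the article gives none for the sample; the prevalences describe the general older population, not activity-center members. The gain is modest, but it is worth taking because it is nearly free.

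**What to change.** State in the analysis section that cognitive frailty status at months 3 and 6 is compared between arms in a model suited to a categorical outcome, logistic for merged status or ordinal for the three levels of Table 1. Adjust for the baseline number of Fried criteria, or at minimum the entry category, and report the effect as a standardized risk difference. Fix this before the outcome data are compared by arm, so that the choice of covariate cannot be seen as a response to the result.

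Leave the allocation as it is. The cost is a sentence or two in the plan. The covariate is already collected at screening, and no extra participants, visits or staff are needed.

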**Figure 1 F1:**
[figure not shown]
Flow diagram of the WE-RISE trial.

##### Intervention

*Experimental Group* The 24-week (6 months) intervention was divided into two phases. Phase 1 comprised of the first 12 weeks whereby an instructor guided group-based intervention was conducted at PAWE centers twice a week for a duration of 90 min per session. Phase 2 comprised of the following 12 weeks whereby the “WE-RISE at Home” is independently carried out by the participants as a home-based intervention.

At the commencement of the WE-RISE intervention, the therapist explained each component of the intervention and what was expected during each intervention session. The 12 weeks of intervention was divided into 3 parts: Level 1 – week 1 – 4, Level 2 - week 5 to 8 and Level 3 – week 9 to 12 with increasing level of intensity for the exercises and cognitive training.

*Multi-component exercise training*. The frequency, intensity, time and type (FITT) principle for this study was established based on best available recommendation for effective exercise interventions among community dwelling older persons with frailty (26). The FITT framework also corroborates with the gold standard guidelines established by the American College of Sports Medicine (ACSM) for exercise prescription in older persons (41). The exercise regime of this intervention is as outlined in detail in Tables 2–5. The exercise training begins and ends with flexibility training consisting of mobility and dynamic stretching of major joints as a warm-up and cool down. This component of the exercise program remains unchanged throughout Level 1–3 (Table 2). Aerobic training is administered through dance aerobic sessions. The dance aerobics will largely comprise of active movements such as stationary march, front and backward march, side walking with a turn, toe steps, in combination with upper and lower limb movements (Table 3). Progressive resistance training targeted upper limb, lower limb and body weight exercises to improve overall muscle strength. The exercises carried out from level 1 to level 3 are maintained throughout with variation in level of resistance and repetitions per set for each exercise. Resistance in this intervention is provided with the usage of weight cuffs (Table 4). The balance and coordination training include multi-task exercises which recruit not just postural control and strength muscles, but also requires cognitive processing (Table 5). A PVC elastic ball is used for part of the balance exercises.

**Table 2 T2:** Flexibility training program.

	**Level 1**	**Level 2**	**Level 3**
*Flexibility: joint mobility & dynamic stretching*	Duration of exercise:10 min		
Head and Neck Shoulder and Arm, Trunk	Repetition: 8 counts for each plane of motion for mobility		
Hip and Knee, Ankle	Stretching: Each stretch sustained for 8 s in each plane of motion		

**Table 3 T3:** Aerobic training program.

	**Level 1**	**Level 2**	**Level 3**
*Aerobic training*	Duration of Exercise: 15 min		
	Type: Dance Aerobics		
	Intensity: RPE 3–5; moderate intensity		Intensity: RPE 6–8; vigorous intensity.

*RPE, Rate of Perceived Exertion*.

**Table 4 T4:** Progressive resistance training program.

	**Level 1**	**Level 2**	**Level 3**
*Progressive resistance training*	Duration of exercise: 30–40 min		
	Number of muscle groups: 8–10		
Upper body strength	Repetition: 8 Number of sets: 3 Weight cuff: 0.5 kg around wrist.	Repetition: 10Number of sets: 3 Weight cuff: 1.0 kg around wrist.	Repetition: 12 Number of sets: 3 Weight cuff: 2.0 kg around wrist.
Shoulder press			
Lateral shoulder raise			
Front shoulder raise			
Triceps extension			
Bicep curl			
Lower body strength	Repetition: 8 Number of sets: 3 Weight cuff: 0.5 kg around ankle.	Repetition: 10Number of sets: 3 Weight cuff: 1.0 kg around ankle.	Repetition: 12 Number of sets: 3 Weight cuff: 2.0 kg around ankle.
Seated knee raise			
Seated knee extension			
Standing hamstring curl			
Standing lateral leg lift			
Calf raises			
Heel raises			
Sit to stand Half-squat (with support)	Repetition: 8 Number of sets: 3 Weight cuff: 0.5 kg around wrist.	Repetition: 10 Number of sets: 3 Weight cuff: 1.0 kg around wrist.	Repetition: 12 Number of sets: 3 Weight cuff: 2.0 kg around wrist.

**Table 5 T5:** Balance and coordination training program.

	**Level 1**	**Level 2**	**Level 3**
Weight shifting	Side to side, frontward to backwards, 8 reps, with support.	Side to side, frontward to backwards, 10 reps, no support.	Side to side, frontward to backwards, 12 reps, no support.
Single leg stand	10 s each leg, with support.	10 s each leg, without support.	10 s each leg, without support.
Semi-tandem stand	10 s, eyes open, with support	10 s, eyes open/closed, with support.	10 s, eyes open/closed, without support.
Tandem stand	10 s, eyes open, with support	10 s, eyes open/closed, with support.	10 s, eyes open/closed, without support.
Sideways walking	10 steps, 4 reps, with support.	10 steps, 4 reps, without support.	10 steps, 4 reps, without support.
Backward walking	10 steps, 4 reps, with support.	10 steps, 4 reps, without support.	10 steps, 4 reps, without support.
Walking with a turn	Walk and turn in the figure 8	Walk and turn in the figure 8	Walk and turn in the figure 8
Heel walking	10 steps, 4 reps, with support.	10 steps, 4 reps, without support.	10 steps, 4 reps, without support.
Toe walking	10 steps, 4 reps, with support.	10 steps, 4 reps, without support.	10 steps, 4 reps, without support.
Ball activity	Ball dribbling and throwing upwards & single direction ball throwing with partner.	Ball dribbling and throwing upwards with one hand; ball throwing/catching in different directions in a stationary circle.	Ball dribbling and throwing upwards with one hand; throwing/catching ball in different directions while rotating in circle.
Tandem walk	10 steps, 4 reps, with support.	10 steps, 4 reps, with support.	10 steps, 4 reps, without support.
Slalom walking	Slalom walk around stationary obstacles.	Slalom walk around stationary obstacles in haphazard directions.	Slalom walk around while picking up stationary obstacles in haphazard directions.
Coordination training	Hand eye coordination training		

There may be a risk of injury involved while participating in physical activity. Older adults are susceptible to injuries such as sprains, repetitive strain, falls, muscle fatigue, muscle cramps or may be hesitant due to fear of injury (60). To overcome these adverse outcomes, safety is ensured at all times by carrying out the activity in the presence of support (chair or wall). Intermittent breaks are provided throughout the exercise regime and hydration is a priority. Participants are arranged in a manner whereby each individual is in the view of the instructor and vice versa. Participants will be briefed that they may experience some form of delayed onset muscle soreness (DOMS) due to muscle adaptation to exercise which is normal and will cease (61). Participants are also advised to rest should they feel pain, discomfort or intolerance to the exercises.

*Cognitive training*. The activities in the intervention will include “paper and pencil tasks,” puzzle activities, memory games, “spot the difference,” coloring activities, matrix reasoning, maze activities and sorting activities as outlined in Table 6. Materials for the cognitive training include, stationary, cognitive challenge worksheets, jigsaw puzzle, memory cards, colored ice cream sticks and colored toothpicks. The level of difficulty will be increased each month to further challenge the participants' cognitive function.

**Table 6 T6:** Outline and description of cognitive training program.

**Activity**	**Domain of Cognition**	**Description of Activity**	**Levels of Difficulty**
“Getting ‘jiggy’ with it” - Jigsaw puzzle	Visuospatial reasoning & working memory	Assembling jigsaw puzzle.	Level 1: 6 Piece puzzle Level 2: 6 Piece & 9 Piece puzzle. Level 3: 6,9- and 12-piece puzzle.
“Let's get it sorted” - Sorting game	Executive function & cognitive flexibility	Sorting different objects by color first and then progressing to sorting by name of color.	Level 1: Ice cream stick and sort only 2 colors. Level 2: Ice cream Stick sort but color of stick or tub. Level 3: Matchstick sort by color of stick and color of tub.
“It's not the same!” - Spot the difference	Attention & processing speed	Two similar pictures are printed on a single sheet. Participants are to spot and circle 10 differences between the two.	Increasing level of complexity of the worksheets provided.
“Get out!” - Maze Activity	Problem solving skills & reaction time	Maze activities printed on paper. Participants are to find their way out of the maze with a pencil.	Increasing level of complexity of the mazes provided.
“What did you see?” - Recall activity	Short term memory	Show a picture for 30 s, remember all the objects within the picture and list as many as possible.	Level 1: 5 objects Level 2: 10 objects Level 3: 15 objects
“Jog that memory” - Memory games with cards.	Reaction time, attention & processing speed	This is a card-based memory game. A deck of cards containing paired pictures is used to play memory-based games such as “snap” or quick pairing.	Level 1: 2 players, 1 deck of cards Level 2: 4 players, 2 deck of cards Level 3: All participants together, combination of 3 different decks.
“Color codes”	Concentration & matrix reasoning	These games are a combination of colors and shapes on paper. Simple sudoku type activity will be given, instead of numbers with shapes of different colors.	Level 1: Only 1 empty spot in each row. Level 2: 2 empty spots in each row. Level 3: Multiple missing spots to be filled.

*Dietary Counseling*. A qualified clinical dietitian conducts a one-off group dietary counseling session which includes the distribution of a dietary information pamphlet to promote physical and cognitive well-being. The pamphlet includes meal by meal guidance and healthy eating habits to be practiced pre- and post- exercise. Participants are encouraged to contact the dietician via phone call should they have any queries.

*Psychosocial support*. Intervention is conducted as a group-based activity which are enjoyable and interesting with constant facilitation. Elements of group-based sessions encompass friendly interaction, support based communication and the establishment of a non-threatening environment to ensure adherence to intervention and improve self-esteem (62). It should be noted that, all activities in the multi-domain intervention excludes competitive components.

*Home based program – “WE-RISE at home”*. Following the completion of the 12-week center based WE-RISE program, the participants were instructed to carry out the intervention in the comfort of their home independently twice a week for 12 weeks. A “WE-RISE at Home” packet containing an activity manual, dietary guideline, 12 sheets of cognitive training activities, 2 sets of jigsaw puzzle, a ball, a pair of 2 kg weight cuffs and stationery, is given to each participant. The manual contains illustrated and written, step-by-step instructions on how to carry out the exercises while ensuring safety at all times. Each participant was provided with a calendar in the manual with scheduled dates to carry out the home program and they were asked to tick the date boxes after completing each session which served as a log for record keeping. Although participants were to stick to the exercises and cognitive activity included in the “WE-RISE at Home”; they were given the autonomy to decide the type of aerobic exercise they preferred to carry out (a choice of: dance aerobics, brisk walking, stationary or mobile jogging, stationary march). They were also able to select which cognitive activity they felt like tackling for each session. Empowerment strategies have been found to play a vital role in bringing forth positive health outcomes and making informed health decisions (63). Participants were contacted every 2 weeks via phone call as an empowerment method aimed to provide social support, motivation, promote positive health behaviors and create awareness of self-efficacy. In addition, it also enabled monitoring of the participants' compliance to the intervention and their health status as the intervention progressed.

*Control group*. The control group in this study received usual care and participate in PAWE weekly conducted community activities such as cooking classes, karaoke, arts and craft, chair exercises, with no changes made to their habitual routine of daily life.

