The domains of cognition namely short-term memory, attention, information processing skills, perceptual organizational tasks, reasoning and logic, and problem-solving abilities were selected for cognitive training in our present intervention. This selection was based on the existing literature among older adults with cognitive impairment (23, 31, 43). We included “Pen to Paper” tasks such as “spot the difference,” mazes, matrix reasoning, and jigsaw puzzles. These tasks have been included as cognitive training resulting in enhanced cognitive function as it tackles multiple domains of cognition (visual perception, orientation perceptual reasoning, cognitive speed), and promotes an increase of brain reserve whilst preventing emotional distress which negatively impacts cognitive aging (23, 44). We deduce that this hands-on approach of cognitive training is not only effective in improving cognitive function but also beneficial in promoting social engagement as an activity of leisure.

For nutritional intervention, the existing interventions to address cognitive impairment or frailty consist of a wide range including a variety of supplementation, specialized diet and single or multi-nutrient intervention (33, 45, 46). As an alternative, dietary counseling, an inexpensive, and straightforward intervention and has been found to substantially reduce the risk of malnutrition among older adults (33). Hence, dietary counseling with education on healthy eating habits was opted as the nutritional intervention in our present study to allow older persons to sustain their healthy eating patterns as it is personalized to locally available and affordable produce.

Group directed intervention was the choice for the delivery of our present multi-domain intervention. This is because it is known to promote social participation, besides improving adherence to physical activity, psychological factors and social relationships; which further advocates that group-based intervention is key as a means of incorporating psychosocial well-being among older adults (47).

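### The intervention is delivered in groups, but the stated repeated measures ANOVA has no session-group term; if outcomes correlate within groups, the standard error is too small

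*Protocol article*

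**What the plan says.** All references are to the Protocol article.

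- **Allocation** (Randomization): individuals are the unit. "Simple randomization was executed using the Research Randomizer computer program by the primary research coordinator". There is more than one centre: "an arrangement was made with the participating PAWEs to allow private and scheduled use of the facility on days". No stratification is named.
- **Delivery** (Intervention, Experimental Group): in the first 12 weeks, "an instructor guided group-based intervention was conducted at PAWE centers twice a week for a duration of 90 min per session". The second 12 weeks are done alone at home.
- **Role of the group** (Development and Selection of Specific Intervention): "Group directed intervention was the choice for the delivery of our present multi-domain intervention", on the grounds that it helps social participation and adherence. The psychosocial component is itself delivered this way: "Intervention is conducted as a group-based activity which are enjoyable and interesting with constant facilitation". Participants also work directly with one another in the ball exercises (Table 5) and the card memory games (Table 6).
- **Controls** (Control group): usual care and their habitual centre activities. The trial forms no group for them.
- **Analysis** (Data Analysis): "Results of the randomized controlled trial will be analyzed using repeated measures analysis of variance for pre-test (Baseline Scores) and post-test" at months 3 and 6, with Bonferroni-corrected post-hoc tests. On the error rate: "An alpha level of (0.05) was considered for all the statistical tests used in the study". No centre or session-group term is named.

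**The concern.** The article expects group members to affect one another and then names a model that assumes they do not. The repeated-measures part of the ANOVA covers only the several measurements on one person. Two people who attended the same sessions for 12 weeks enter as unrelated observations.

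If a group does better or worse as a whole, through its atmosphere, attendance or mix of members, ten people in one group carry less information than ten people treated separately. The ANOVA would then report intervals that are too narrow and p-values that are too small. The error runs towards a false claim that cognitive frailty has been reversed.

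**Working it through.** **Inputs from the article.** Two-sided alpha of 0.05 and 80% power (Data Analysis); individual simple randomisation (Randomization); trial-formed groups in the intervention arm only (Intervention). The article gives no sample size, group size, number of groups or ICC, so there is no figure of its own to reproduce.

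**Assumptions.** Equal arms of size n; m people per session group; ICC ρ for the quantity compared between arms; no clustering among controls; one continuous comparison at one follow-up time.

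**Formulas.**

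1. Variance of the intervention mean: (σ²/n) × DE, with DE = 1 + (m − 1)ρ. Variance of the control mean: σ²/n.
2. The ANOVA in effect uses 2σ²/n for the difference. True over assumed variance: R = (DE + 1)/2. The SE ratio is √R.
3. Actual two-sided alpha = 2 × [1 − Φ(1.96/√R)].
4. Power with a correct SE, if the trial had been sized for 80% under independence: Φ[(1.96 + 0.842)/√R − 1.96].

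**Example, m = 10, ρ = 0.05.** DE = 1 + 9 × 0.05 = 1.45. R = 2.45/2 = 1.225. √R = 1.107. 1.96/1.107 = 1.771, so alpha = 7.7%. Power = Φ(2.802/1.107 − 1.96) = Φ(0.571) = 72%.

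| m | ICC | DE | R | SE ratio | Actual alpha | Power with correct SE |
|---|---|---|---|---|---|---|
| any | 0 | 1.00 | 1.000 | 1.000 | 5.0% | 80% |
| 5 | 0.01 | 1.04 | 1.020 | 1.010 | 5.2% | 79% |
| 8 | 0.02 | 1.14 | 1.070 | 1.034 | 5.8% | 77% |
| 10 | 0.05 | 1.45 | 1.225 | 1.107 | 7.7% | 72% |
| 10 | 0.10 | 1.90 | 1.450 | 1.204 | 10.4% | 64% |
| 20 | 0.05 | 1.95 | 1.475 | 1.214 | 10.7% | 64% |
| 20 | 0.10 | 2.90 | 1.950 | 1.396 | 16% | 52% |

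**Simulation.** 20,000 runs per setting, simple individual randomisation, 20 people per centre, the treated people in each centre forming one group (10 on average), and a two-sample test that ignores centre and group.

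- Group effect only, ICC 0.05: rejection rate 8.1% with 5 centres (empirical SE 0.226 against a reported 0.200) and 7.7% with 8 centres.
- Group effect only, ICC 0.10: 10.7% with 5 centres and 10.5% with 8.
- Centre effect shared by both arms, ICC 0.05 or 0.10, no group effect: 4.8% to 5.2%, with empirical and reported SE about equal.
- Same centre effect, ICC 0.10, 5 centres, arms balanced within centre: 4.2%.

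The inflation therefore comes from the session group. A centre effect common to both arms does not produce it.

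**The case against.** The strongest reply is that within-group correlation is not shown. No ICC is reported, one physiotherapist delivers the exercise, cognitive and psychosocial parts (Intervention Providers), the programme is standardised (Tailoring) and delivery is observed (Adherence/Fidelity). An instructor common to all groups adds no variance between groups, and standardisation limits it. Half of the intervention period is spent working alone at home, so correlation at month 6 may be weaker than at month 3. All of this stands. It makes the size uncertain and the point conditional, but it does not make independence a safe assumption when the group is an intended ingredient.

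A second reply is that controls also meet at the centres, so clustering in one arm only is itself an assumption. That is so. Correlation peculiar to the controls would add variance, however, so leaving it out does not exaggerate the problem.

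A third is that an article condenses, and an analysis plan not at hand may add a group term. It may. But the article names its model, and a repeated measures ANOVA does not ordinarily carry a random group effect.

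A reader might also infer that simple randomisation, or leaving centre out of the model, makes the standard error too small. The documents do not support this. Individuals are randomised, and a centre effect shared by both arms left the error rate at or below nominal in the simulation. Simple randomisation is valid; it allows chance imbalance by centre or baseline category, which is a matter of precision and not of bias.

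**Conclusion.** The point holds in conditional form. The stated model has no term for the session groups in which the intervention arm is treated, so if the within-group ICC is above zero the standard error is understated and the 0.05 level is not kept. Under the assumptions listed, actual alpha runs from 5.2%, which is negligible, through 7.7% to 16%, which is serious. It is exactly 5% at an ICC of zero. The article does not allow a choice within that range, because group size, number of groups and ICC are absent. The figures apply most directly to month 3.

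This is worth correcting but does not invalidate the trial. It is also no ground for asking for stratified allocation: randomisation is described as already executed, so only the analysis can change.

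**What to change.** 1. Record a session-group identifier for every intervention participant.
2. Replace the repeated measures ANOVA with a partially nested mixed model: a random session-group effect in the intervention arm only, correlation within person over time, and small-sample degrees of freedom such as Satterthwaite. SPSS, the software already named, fits mixed models.
3. Use the matching random effect in the model for the categorical primary outcome.
4. Adjust every model for PAWE and for baseline category (cognitive pre-frailty or cognitive frailty). This is for precision and for chance imbalance under simple randomisation; it does not replace the group term.
5. If there are few groups, or one per PAWE, the group variance is poorly estimated and cannot be told apart from a centre-by-treatment effect. In that case report the arm comparison over a range of ICC values, for example 0 to 0.10, using the actual group sizes.

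The cost is one extra variable and a somewhat more complex model. The downside is wider intervals, and with few groups very low degrees of freedom.
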